# **Study design**

A single-site, interventional, randomized (1:1), parallel-group, double-blind, controlled, 8-week clinical trial.

Expected study duration: 24 months.

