## *4.1 Inclusion criteria*

- age ≥65 years
- admission for physical rehabilitation
- sarcopenia (according to European Working Group on Sarcopenia in Older People [EWGSOP] criteria in terms of outcome of body composition by bioimpedance analysis [skeletal muscle mass/body weight  100, ≤37% in men and ≤28% in women], handgrip strength and gait speed)
- Mini Mental State Examination (MMSE) ≥18
- Written informed consent (patient or legal guardian)

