## *6.1 Assessments*

The following assessments will be performed throughout the study as indicated above:

*Medical History & Demographics.* Information will be collected on age, gender, main admission diagnosis, number of comorbidities and medications.

*Nutritional Assessment:* body weight (to the nearest 0.1 kg) and height (to the nearest 0.5 cm) will be measured according to standard procedures and body mass index (BMI) will be derived accordingly (*Anthropometry*). A trained dietitian will be responsible for the evaluation of calorie and protein intake. At study inclusion a 24-h dietary recall (with the aid of the caregiver) will be performed with the help of a food atlas, while at the end of study a calibrated dietetic spring scale will be used to weigh all foods served and returned on consecutive days. A computer program (DR3 v3.1.0; Sintesi Informatica Srl, Milano, Italy) will be used to estimate the energy and the macronutrient content of food consumed (*Protein-calorie intake*), including nutritional supplementation. Finally, nutritional status will be rated by means of the *Mini Nutritional Assessment* (MNA®), a brief questionnaire based on an anthropometric assessment (BMI and weight loss), a general assessment (lifestyle, medication, and mobility), and a dietary assessment (number of meals, food and fluid intake, self-assessment of autonomy of eating, and self-perception of health and nutrition).

*Muscle mass (body composition)*: in the screening phase, the presence of low skeletal muscle mass will be diagnosed [(skeletal muscle mass/body weight  100) ≤37% in men and ≤28% in women] using bioelectric impedance analysis (BIA 101; Akern s.r.l., Florence, Italy). Then, appendicular muscle mass (AMM) and total body skeletal muscle mass (for the calculation of skeletal muscle mass index [SMMI]) will be evaluated using Dual-energy X-ray absorptiometry (DXA; Lunar Prodigy, GE Medical Systems).

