# **Statistics and sample size**

***8.1 Sample size***

In the absence of preliminary data to estimate the expected treatment difference, the sample size was set at 128 patients reaching the evaluation of the primary endpoint (64 per arm) to achieve a statistical power of 80% (type I error 5% using a two-tailed test) to detect a clinically meaningful difference (mean treatment difference/standard deviation [effect size]=0.5). Allowing for a 10% drop-out rate in each arm, it was decided to randomize 140 patients (70 per treatment arm).

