***8.2 Statistical analysis***

The efficacy analysis population will include the patients reaching the primary endpoint evaluation and it will be performed according to the intention to treat principle.

All patients consuming at least one serving of nutritional formula will be included in the safety analysis.

Descriptive statistics: Mean and standard deviation, range, median and quartiles will be calculated for continuous variables. Frequencies and percentages will be calculated for categorical variables.

Analysis of study endpoints: Expecting a treatment effect also on the LOS, changes over time in both primary and secondary continuous outcome variables will be normalized by the duration of observation in months. Changes will be calculated so that an improvement would result in a positive value in favor of the experimental formula (as either final - initial value or initial - final values).

*Primary endpoint* - The change in gait speed will be compared between groups with a generalized linear regression model using Huber-White robust standard errors to account for variance inhomogeneity. Then a series of supportive analyses of the primary endpoint will be performed. First, we will conduct a multivariable model, to adjust for potential confounders regardless of differences in baseline features, including gender, age and monthly change in energy intake, creatinine and in total cholesterol. Second, a conservative sensitivity analysis of the primary endpoint using the worst possible outcome of the study for patients dropping out will be performed.

*Secondary endpoints* - Group comparison will be performed for all secondary endpoints on a continuous scale using an unadjusted generalized linear regression model. For both primary and secondary outcome variables the mean change within groups will be also assessed. For secondary endpoints on a binomial scale, a generalized linear model for the binomial family will be used. For all endpoints the treatment effect (mean or frequency difference) and 95% confidence interval (CI) will be reported.

All statistical analyses will be performed using the software STATA 15.0 statistical software (Stata Corporation, College Station, TX).

Dropout

The following causes of dropout will be considered:

- Death

- Lost to follow-up (due to hospitalization or transfer to another setting of care)

- Withdrawal

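### Main admission diagnosis is recorded at baseline but named in no model: the planned test stays valid, yet precision and a case-mix robustness check may be forgone

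*Protocol*

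**What the plan says.** - **Population.** The reason for admission is limited only by "admission for physical rehabilitation" (Protocol, 4.1 Inclusion criteria). The exclusions in 4.2 rule out some conditions but do not confine the trial to one rehabilitation diagnosis.
- **Baseline data.** "Information will be collected on age, gender, main admission diagnosis, number of comorbidities and medications" (6.1 Assessments).
- **Allocation.** "A single-site, interventional, randomized (1:1), parallel-group, double-blind, controlled, 8-week clinical trial" (Study design). No stratification factor is named.
- **Primary model.** Section 8.2 compares change in gait speed per month between the arms by regression with Huber-White standard errors and lists no covariate.
- **Supportive model.** Its purpose is to "adjust for potential confounders regardless of differences in baseline features, including gender, age and monthly change in energy intake, creatinine and in total cholesterol" (8.2). Two of these five covariates, gender and age, are baseline variables. The other three are changes over the stay.
- **Secondary continuous endpoints.** Section 8.2 analyses them unadjusted.
- **Sample size.** "the sample size was set at 128 patients reaching the evaluation of the primary endpoint (64 per arm"), for "mean treatment difference/standard deviation [effect size]=0.5" (8.1 Sample size).

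**The concern.** Patients admitted for different reasons may recover walking speed at different rates. If so, diagnosis is a baseline predictor that is already being collected, is fixed before allocation and cannot be affected by the supplement. A model that leaves it out carries the between-diagnosis spread as noise. An imbalance that arises by chance then stays in the realised estimate.

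The supportive analysis is where a reader would look for reassurance on this. As listed, it adjusts for only two baseline characteristics, and neither describes why the patient was admitted. If the arms turned out to differ in case mix, adding diagnosis after the results were known would look data-driven. At stake are some precision in the primary comparison and the ability to answer the case-mix question with a prespecified analysis.

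**Working it through.** **Inputs from the Protocol (8.1).** Two-sided 5% test, 80% power, effect size 0.5, 64 evaluable per arm (N = 128), 140 randomised.

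**Inputs assumed.** The Protocol gives no diagnosis mix, number of categories or link between diagnosis and gait recovery. The share of outcome variance explained (R²), the category count, the prevalence and the recovery gap below are therefore all assumptions.

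**1. Reproduce the plan's figure.** A two-sample t-test at effect size 0.5 needs 63.77 per arm, so 64 per arm and 128 in all. Power at 64 per arm is 80.1%. The stated size is right and does not depend on adjusting for diagnosis. With 140 randomised and 10% dropout, 140 × 0.9 = 126 are evaluable, giving 79.5% power.

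**2. Is the unadjusted test valid when diagnosis matters?** In 40,000 simulated trials at each R² of 0.05, 0.10 and 0.20, with a two-category diagnosis left out of the analysis, type I error was 0.050, mean bias about 0 and power 80.3 to 80.5%. Yes.

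**3. How large could a chance imbalance be?** For a diagnosis group of 40% of patients (assumed), the SE of the between-arm difference in proportion is √(2 × 0.4 × 0.6 / 64) = 0.0866.
- P(difference of at least 10 points) = 0.248.
- P(difference of at least 15 points) = 0.083.

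If recovery differs by 0.5 to 1.0 SD between this group and the rest (assumed), a 10-point imbalance moves the estimate by 0.10 × 0.5 = 0.05 SD to 0.10 × 1.0 = 0.10 SD. The SE of the treatment difference is √(2/64) = 0.177 SD, so the shift is 0.05/0.177 = 0.28 to 0.10/0.177 = 0.57 of one SE, in either direction.

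**4. What would adjustment change?** With q indicator variables for diagnosis, the variance of the treatment difference (in SD² units) is

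(1 − R²) × (4/N) × [1 + q/(N − q − 3)],

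with N − 2 − q degrees of freedom. Power comes from the noncentral t distribution. For four categories q = 3, so the bracket is 1 + 3/122 = 1.0246. At R² = 0.10 the SE ratio to unadjusted is √(0.90 × 1.0246) = 0.960.

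| R² (assumed) | SE ratio, 4 categories | Power, 4 categories | Power, 6 categories (q = 5) |
| --- | --- | --- | --- |
| 0 | 1.012 | 79.2% | 78.5% |
| 0.02 | 1.002 | 80.0% | 79.3% |
| 0.05 | 0.987 | 81.2% | 80.5% |
| 0.10 | 0.960 | 83.2% | 82.6% |
| 0.20 | 0.905 | 87.3% | 86.7% |

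The comparator is 80.1% unadjusted. On variance, four categories break even when (1 − R²) × 125/122 = 1, which is R² = 3/125 = 0.024. Six categories break even at R² = 5/125 = 0.04. The gain therefore depends both on diagnosis being prognostic and on keeping the categories few.

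**The case against.** **The plan contains no error here.** An unadjusted comparison of randomised arms is legitimate. A reader might infer that chance case-mix imbalance biases the primary result. The documents do not support that: under randomisation this variation is already counted in the standard error, the 5% error rate and the planned power. This part of the objection stands in full.

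**The gain is not established.** A reader might also infer that precision is certainly being lost. The Protocol gives nothing on how strongly diagnosis predicts gait recovery, and below an R² of about 0.02 adjustment gains nothing or costs slightly. This stands too, so the point can be put only as a conditional one.

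**Why diagnosis and not something else?** Number of comorbidities, medications, Barthel Index, MMSE and rehabilitation profile are also recorded at baseline and used in no model. The documents do not rank diagnosis above them. The case for it is a judgement: eligibility is open as to the reason for admission, and diagnosis records that reason. It should not be presented as a finding about prognostic strength.

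**A statistical analysis plan may add covariates or describe the randomisation further.** That is possible, and the lack of a named stratification factor is no defect in itself. The word that introduces the covariate list in 8.2 can also be read as leaving it open. Even so, the Protocol does choose to name the covariates of its supportive model, takes two from the same sentence as diagnosis and leaves diagnosis out. That choice can fairly be commented on.

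**Conclusion.** The point holds as an optional efficiency and robustness improvement. Diagnosis is collected, case mix is open and no model in 8.2 names diagnosis, so the supportive analysis as listed cannot show whether the result survives a case-mix imbalance. No stated figure is wrong: the evaluable number, the error rate and the power at 64 per arm all stand.

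Under the assumed range of 0 to 20% of variance explained, adjustment with four categories runs from a loss of 0.9 power points (80.1 to 79.2%) to a gain of 7.2 (80.1 to 87.3%). The middle case of 10% gives about 3 points. The possible gain is larger than the possible loss, but its size rests wholly on a prognostic strength that the documents do not give.

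**What to change.** In 8.2, add main admission diagnosis as a categorical baseline covariate to the supportive multivariable model, and preferably to the primary gait-speed model as well. State the choice outright. Use at most 3 or 4 categories and list them in the text.

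Fix the grouping before any outcome data are reviewed. Fixing it only before treatment codes are attached is not enough: under 7.1 data are entered after each evaluation, and under 7.2 the codes are added after the last patient's last evaluation, so the groups could be chosen with outcomes in view.

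Keep the Huber-White standard errors, the mean difference with 95% CI and the sample size of 128 evaluable patients.

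The cost is one sentence, a short grouping list agreed in advance and up to 3 degrees of freedom. If diagnosis proves not to be prognostic, that is about one power point. No new data are needed.

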***2.3 Other pre-specified study endpoints***

As explorative endpoints, we will also consider changes (per month) in: protein and energy intake, Mini Nutritional Assessment (MNA®) score, C-reactive protein, vitamin D, total cholesterol, albumin and creatinine.

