***5.2 Nutritional intervention***

An individualized dietary program will be drawn up for each patient, taking nutritional and mastication issues, as well as any swallowing issues into consideration. In addition to hospital diet, subjects will be randomly allocated to receive twice daily:

a) Experimental formula: a whey protein-based food for special medical purposes enriched with leucine and vitamin D (Fortifit®, Nutricia). Each serving consists of 40 g of powder (vanilla or strawberry flavor), providing 150 kilocalories and containing 20 g of whey proteins, 2.8 g of leucine, 9 g of carbohydrates, 3 g of fat, 800 IU of vitamin D, and a mixture of vitamins, minerals (calcium, 500 mg), and fibers [17-20].

b) Control formula: an isocaloric formula consisting of 40 g of a flavored (vanilla or strawberry) powder containing maltodextrins.

The intervention formula will be reconstituted with 100-150 mL water and administered at breakfast and in the afternoon. In the event of dysphagia to liquids, the density of the reconstituted formula will be increased, as appropriate.

The actual supplement and control formula will be given in identical containers devoid of any labelling for at least 4 weeks (minimum duration of the rehabilitation) up to 8 weeks (maximum duration of the rehabilitation). Compliance with intake of nutritional interventions will be monitored by recording the number of servings consumed every day in a diary.

1. **Methods**

The assessments and the procedures to be performed throughout the study are summarized in the following table:

| ASSESSMENTS/PROCEDURES | BASELINE | END OF STUDY |
| --- | --- | --- |
| Inclusion/exclusion criteria | X |  |
| Informed consent | X |  |
| Medical history & demographics | X |  |
| Randomization | X |  |
| Anthropometry | X | X |
| Protein-calorie intake | X | X |
| Mini Nutritional Assessment | X | X |
| Physical performance | X | X |
| Physical function | X | X |
| Muscle strength (handgrip) | X | X |
| Muscle mass | X | X |
| Cognitive function | X | X |
| Biochemistry | X | X |
| Quality of life | X | X |
| Complexity of assistance needs | X | X |
| Compliance to nutritional intervention |  | X |
| Safety data |  | X |
| Modality of discharge |  | X |
| Total duration of rehabilitation |  | X |
| Length of stay |  | X |

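### Exploratory intake endpoint: dividing a fixed step in energy intake by months of stay creates a false arm difference when stay differs, and the same quantity enters the supportive gait-speed model

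*Protocol*

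**What the plan says.** Protocol section 6.1 fixes two instruments. At the start, "At study inclusion a 24-h dietary recall (with the aid of the caregiver) will be performed with the help of a food atlas". Later, "at the end of study a calibrated dietetic spring scale will be used to weigh all foods served and returned on consecutive days". The estimated intake is computed "including nutritional supplementation".

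Section 2.3 sets the endpoint: "As explorative endpoints, we will also consider changes (per month) in: protein and energy intake". Section 8.2 gives the reason for working per month: "Expecting a treatment effect also on the LOS, changes over time in both primary and secondary continuous outcome variables will be normalized by the duration". That sentence names primary and secondary outcomes only, but section 2.3 itself puts intake on a monthly scale. Section 6.2 repeats the expectation that treatment affects the duration of stay.

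Under section 5.2 both arms take two servings a day. The experimental serving provides 150 kcal and 20 g of whey protein. The control is "an isocaloric formula consisting of 40 g of a flavored (vanilla or strawberry) powder containing maltodextrins". Sections 5.1 and 5.2 let the programme run from 4 to 8 weeks, depending on progress.

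The quantity has a second use. In section 8.2 the supportive multivariable model for gait speed adjusts for potential confounders "including gender, age and monthly change in energy intake, creatinine and in total cholesterol".

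**The concern.** A change per month is a sensible scale for something that builds up during the stay. Intake of a fixed daily supplement does not build up: it rises once, when the formula starts, and stays there. A systematic difference between a recalled day and weighed food is likewise present once, in full, whatever the length of stay. Dividing such a step by time makes it look larger in patients who leave early and smaller in those who stay.

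If treatment shortens stay, as the protocol expects, two arms with identical energy intake at both times would be reported as different. A reader could then see an energy imbalance between formulas that were designed to be isocaloric. The same distorted quantity is a covariate in a model of gait speed, an outcome that is itself divided by stay.

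There is also a lesser problem from the mixed instruments. Subtracting one recalled day adds that day's noise to the comparison, and a before-after figure within one arm would mix true change with an instrument difference of unknown size and sign.

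**Working it through.** The protocol states no expected value or precision for intake, so there is no figure of its own to reproduce here.

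**Inputs from the protocol**
- Formula energy: 2 × 150 = 300 kcal/day in the experimental arm, and the same in the control arm because the control is isocaloric (5.2). Full consumption is assumed in both arms.
- Formula protein, experimental arm: 2 × 20 = 40 g/day (5.2).
- Stay: 4 to 8 weeks (5.1, 5.2), expected to depend on treatment (6.2, 8.2).

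**Assumptions, not in the protocol**
- Illustrative stays of 5 weeks (experimental) and 6 weeks (control).
- Recall error from 300 kcal/day too high to 300 kcal/day too low.
- One month = 30.44 days.

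**Formula.** Let b be the net step between the baseline and final values, the same in both arms, and T the stay in months. The undivided arm difference is b − b = 0. The difference in monthly change is b(1/T_exp − 1/T_ctrl). If stays vary within an arm, the mean of 1/T takes the place of 1/T.

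**Formula step alone, b = 300.** T_exp = 35/30.44 = 1.15 and T_ctrl = 42/30.44 = 1.38 months. Then 300/(35/30.44) = 260.9 and 300/(42/30.44) = 217.4. The false difference is 43.49 before rounding, about 43 kcal/day/month.

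**With recall error, same stays**

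| Recall reads | Net step b (kcal/day) | False arm difference (kcal/day/month) |
|---|---|---|
| 300 too high | 0 | 0 |
| 150 too high | 150 | 22 |
| correctly | 300 | 43 |
| 150 too low | 450 | 65 |
| 300 too low | 600 | 87 |

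**Other stays, b = 300**

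| Control vs experimental stay | False arm difference (kcal/day/month) |
|---|---|
| 8 vs 8 weeks | 0 |
| 8 vs 7 weeks | 23 |
| 8 vs 6 weeks | 54 |
| 8 vs 4 weeks | 163 |

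**Real differences are rescaled too.** A constant 40 g/day of formula protein is reported as 40/(28/30.44) = 43.5 g/day/month after 4 weeks and 40/(56/30.44) = 21.7 after 8 weeks. The same exposure is halved by stay alone.

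**Noise from subtracting the recall (illustration).** Assume a between-person SD of 15 g protein, a day-to-day SD of 20 g and 3 weighed days. The end value has variance 15² + 20²/3 = 358. The undivided change has variance 2 × 15²(1 − ρ) + 20² + 20²/3, where ρ is the correlation between a person's usual intake at the two times. This is 533 for ρ = 1 and 758 for ρ = 0.5, or 1.5 and 2.1 times the variance of the end value.

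**The case against.** The case for leaving this alone has real weight.

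- **Two instruments do not by themselves bias a randomised comparison.** An offset common to both arms cancels from the undivided change. This stands: the division by months causes the arm bias, and would do so even with one perfect instrument.
- **The endpoint is exploratory.** No power claim or efficacy conclusion rests on it, and the protocol does not make it the proof that the arms differed in protein but not energy. Formula composition sets that contrast, and a daily diary of servings tracks consumption. This stands and limits the weight of the point.
- **The size depends on unknowns.** The protocol gives no recall error and no expected stays. A recall that reads 300 kcal too high would cancel the formula step exactly. This stands, which is why the range starts at zero.
- **No within-arm intake change is expressly planned.** Section 8.2 plans within-group change for primary and secondary outcomes only. This stands; the caution applies to any such figure that might be reported.

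A reader might also infer that the baseline recall describes eating at home and the final weighing the ward diet. Caregiver help and a food atlas make that plausible, but section 6.1 does not say what setting the recalled day covers. The arm bias does not depend on it.

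The objection does not remove the central fact. The formula step is built into both arms, it does not accumulate, and it is to be divided by a duration that treatment is expected to change.

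**Conclusion.** The point holds in a limited form. As defined, monthly change in energy intake will generally show a false arm difference when stay differs between arms. It is zero only if stays are equal (strictly, if the mean of 1/T is equal) or the net step is zero, so it is too strong to say that the arms must differ whenever stay differs. The size is about 43 kcal/day/month from the formula step alone, and about 0 to 87 over the recall errors considered, for assumed stays of 5 and 6 weeks and full consumption in both arms. For protein, the reported difference depends on stay as well as on intake.

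An undivided arm comparison would not be biased by the common offset, but subtracting the recall can add noise and would leave any within-arm intake change uninterpretable.

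A reader might infer that the trial's main result is compromised. It is not: the unadjusted comparison of gait speed does not use intake. The contact with the primary endpoint is the supportive adjusted model, where the quantity is measured after randomisation and shares the divisor 1/T with the outcome. The sponsor should correct this, but it does not put the primary analysis in doubt.

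**What to change.** In sections 2.3 and 8.2, define the intake endpoint as end-of-study weighed intake (g protein/day and kcal/day, formula included) compared between arms. Use the baseline recall as a covariate or a descriptor. Do not divide by months, and do not interpret a within-arm change in intake.

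In the supportive gait-speed model in section 8.2, replace the monthly change in energy intake with the baseline intake value.

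Dropping the division alone would already remove the arm bias. Using the end value also avoids the mixed-instrument change score.

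The cost is small. All the data are already to be collected, but this is not purely a wording change: one covariate in a pre-specified supportive model is replaced, and no change-from-baseline figure for intake is reported.

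### Dividing the change in protein and energy intake by months of stay turns a one-off step, measured with two different instruments, into a figure that depends on length of stay

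*Protocol*

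**What the plan says.** Section 2.3 lists the endpoint among the explorative ones: "we will also consider changes (per month) in: protein and energy intake".

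Section 6.1 uses one method at each time point. At baseline: "At study inclusion a 24-h dietary recall (with the aid of the caregiver) will be performed with the help of a food atlas". At the end: "while at the end of study a calibrated dietetic spring scale will be used to weigh all foods served and returned on consecutive days". The number of weighed days is not given. Intake is computed "including nutritional supplementation". The schedule table in the Methods section has only these two measurements.

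Section 5.2 fixes the formula: "In addition to hospital diet, subjects will be randomly allocated to receive twice daily". An experimental serving supplies 150 kcal and 20 g of whey protein. The control is described as isocaloric, and maltodextrins are its only named content.

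Section 5.1 lets the programme run from 4 to 8 weeks according to results. Sections 6.2 and 8.2 say that a treatment effect on length of stay is expected, and give this as the reason for dividing changes by months. Section 8.2 also puts the monthly change in energy intake into the supportive adjusted model of the primary endpoint.

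**The concern.** A per-month rate suits a quantity that builds up over time. Daily intake from a fixed supplement does not: it rises when the formula starts and then stays roughly level. The shift from a recalled day to weighed food is also a one-off, and so is any change that comes with the hospital diet. Dividing these steps by months makes the same daily intake look smaller the longer the patient stays.

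Stay depends on response and is expected to differ by arm, so the divisor can create an arm difference in energy where none exists. It can also distort the protein difference that the formula is meant to produce. At stake is the trial's only direct measure of how much extra intake was achieved. The energy variable carries the problem into the supportive model, where covariate and gait-speed outcome share the same divisor.

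**Working it through.** The protocol gives no expected figure for intake, so there is none to reproduce. The check asks what the stated rule returns when daily intake is the same.

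**Inputs from the protocol**
- Two servings a day (5.2): 2 × 150 = 300 kcal/day in either arm, and 2 × 20 = 40 g/day of protein in the experimental arm.
- Stay of 4 to 8 weeks (5.1).
- 64 evaluable patients per arm (8.1).

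**Assumptions**
- A month is 365.25/12 = 30.4375 days, or 4.348 weeks.
- All servings are taken, ordinary food is not displaced, and the change is a pure step.
- The difference in stay, the total step and the intake SD are not in the protocol and are varied below.

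**Formula.** For a step D and a stay of w weeks, the per-month value is D × 4.348 / w.

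| Stay (weeks) | 4 | 5 | 6 | 7 | 8 |
|---|---|---|---|---|---|
| +300 kcal/day, read per month | 326 | 261 | 217 | 186 | 163 |
| +40 g/day protein, read per month | 43.5 | 34.8 | 29.0 | 24.8 | 21.7 |

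The same daily intake spans a twofold range.

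**False energy contrast.** With the same D in both arms and stays w1 and w2, the contrast is D × 4.348 × (1/w1 − 1/w2). For D = 300:
- 5 versus 6 weeks: 300 × 4.348 / 30 = about 43 kcal/day per month.
- 5 versus 7 weeks: about 75.
- 4 versus 8 weeks, the extreme: 163.

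The true step also contains the instrument shift and the move to hospital food, whose sizes are unknown. Total steps of 100, 300 and 500 kcal/day give about 14, 43 and 72 at 5 versus 6 weeks. The arm with the shorter stay shows the larger value if the step is positive.

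**Simulation.** There were 3,000 trials with 64 patients per arm, a normally distributed step with the same mean in both arms, assumed stays uniform on 4–7 versus 5–8 weeks, and Welch tests at 5% two-sided.

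| Mean step (kcal/day) | SD | False positives, divided | False positives, undivided |
|---|---|---|---|
| 0 | 300 | 5.2% | 5.1% |
| 0 | 500 | 5.1% | 5.2% |
| 300 | 300 | 15.8% | 4.9% |
| 300 | 500 | 8.9% | 5.7% |
| 500 | 300 | 33.7% | 5.2% |
| 500 | 500 | 16.3% | 4.8% |

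With equal stays (uniform on 4–8 weeks in both arms) the divided analysis gives 4.8% to 5.8%. The false contrast therefore needs both a non-zero step and unequal stays.

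**Instrument shift.** In a randomised comparison the recall-to-weighing shift should be alike in both arms and cancel in an undivided contrast. After division by unequal stays it no longer cancels.

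**The case against.** The case on the other side has force. The endpoint is explorative, and neither the unadjusted primary analysis nor the sample size depends on it. The instrument shift is no separate bias between arms, since it cancels but for the divisor. The protocol gives no size for the effect on stay and no intake SD, so the 43 kcal figure and the false-positive rates illustrate and do not predict. Food intake may also drift during the stay, so the change need not be a pure step. The choice of model for an explorative variable could be left to an analysis plan. All of this limits the size of the point. It does not remove it, because section 2.3 itself fixes the per-month form and section 6.1 the two instruments.

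A reader might infer more than the documents support:
- **That the baseline recall describes diet at home.** Section 6.1 says only that it is done at inclusion with a caregiver's help.
- **That artefactual within-group changes in intake are planned.** Section 8.2 plans within-group change for primary and secondary variables, and intake is neither.
- **That the figure contains no intake change at all.** It mixes a true change with a shift of method and setting.
- **That computing intake unblinds staff.** Energy needs no knowledge of the arm, because the formulas are isocaloric. Protein from the formula does depend on the arm, but section 6.1 does not say who adds it or when. Section 7.2 joins masked codes after the last evaluation. Nothing says that the dietitian who assesses intake is the one who enters data under section 7.1. With progressive data entry in a trial described as "parallel-group, double-blind, controlled", the order of steps needs stating, but a breach is not shown.

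**Conclusion.** The point holds as a minor one. Per-month scaling is wrong for an intake that moves as a step and is measured with a different instrument at each end. For energy it can produce a false difference between isocaloric arms: about 43 kcal/day per month at an assumed 5 versus 6 weeks with a 300 kcal/day step, and 14 to 72 for steps of 100 to 500. For protein, where the arms are meant to differ, it rescales a real difference by stay, so that 40 g/day reads as anything from 43.5 to 21.7. These sizes rest on the assumed stays, full intake of servings and a pure step; with equal stays or no step the false contrast vanishes. The only effect on a primary-endpoint analysis is through the energy covariate in the supportive adjusted model.

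**What to change.** - **Sections 2.3 and 6.1:** compare end-of-study weighed intake (kcal/day and g/day) between arms with the baseline recall as covariate, and do not divide by months. As a covariate, the recall only has to predict later intake; it need not be on the same scale as the weighed record. State that the raw end-minus-baseline difference is not to be read as a pure change in intake.
- **Section 8.2:** replace the monthly change in energy intake in the supportive model with baseline intake.
- **Sections 3, 6.1, 7.1 and 7.2:** state that the dietitian records food, and that the formula's content is added by program from the serving diary after the treatment codes are joined. This makes the four sections agree.

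No extra measurement is needed. The costs are that intake including the formula becomes available only after the codes are joined, and that one covariate in the supportive model is respecified. The comparison then describes intake at the end of each patient's stay; if food intake drifts over time, two measurements cannot separate that drift.
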